## Abstract

**Background:**

This study will assess measures of vascular health and inflammation in Aboriginal Australian adults with chronic kidney disease (CKD), and determine if intensive periodontal intervention improves cardiovascular health, progression of renal disease and periodontal health over a 24-month follow-up.

**Methods:**

The study will be a randomised controlled trial. All participants will receive the periodontal intervention benefits, with the delayed intervention group receiving periodontal treatment 24 months following baseline. Inclusion criteria include being an Aboriginal Australian, having CKD (a. on dialysis; b. eGFR levels of <60 mls/min/1.73 m^2^ (CKD Stages 3 to 5); c. ACR ≥30 mg/mmol irrespective of eGFR (CKD Stages 1 and 2); d. diabetes plus albuminuria (ACR ≥ 3 mg/mmol) irrespective of eGFR), having moderate or severe periodontal disease, having at least 12 teeth, and living in Central Australia for the 2-year study duration. The intervention involves intensive removal of dental plaque biofilms by scaling, root-planing and removal of teeth that cannot be saved. The intervention will occur in three visits; baseline, 3-month and 6-month follow-up. The primary outcome will be changes in carotid intima-media thickness (cIMT). Secondary outcomes will include progression of CKD or death as a consequence of CKD/cardiovascular disease. Progression of CKD will be defined by time to the development of the first of: (1) new development of macroalbuminuria; (2) 30 % loss of baseline eGFR; (3) progression to end stage kidney disease defined by eGFR <15 mLs/min/1.73 m^2^; (4) progression to end stage kidney disease defined by commencement of renal replacement therapy. A sample size of 472 is necessary to detect a difference in cIMT of 0.026 mm (SD 0.09) at the significance criterion of 0.05 and a power of 0.80. Allowing for 20 % attrition, 592 participants are necessary at baseline, rounded to 600 for convenience.

**Discussion:**

This will be the first RCT evaluating the effect of periodontal therapy on progression of CKD and cardiovascular disease among Aboriginal patients with CKD. Demonstration of a significant attenuation of CKD progression and cardiovascular disease has the potential to inform clinicians of an important, new and widely available strategy for reducing CKD progression and cardiovascular disease for Australia’s most disadvantaged population.

**Trial registration:**

This trial is registered with the Australian New Zealand Clinical Trial Registry ANZCTR12614001183673.

## Background

### Aboriginal Australian health

Aboriginal Australians experience poor health relative to their non-Aboriginal counterparts [1]. They have 15–20 years shorter life expectancy, much higher levels of chronic diseases, and are more likely to experience disability and reduced quality of life due to ill health. There is a heavy burden of infectious diseases as well as high rates of metabolic risks among the Aboriginal population [2]. Along with other chronic conditions, dental disease and chronic kidney disease levels in the Aboriginal population are equivalent to those in the poorest nations [3, 4]. There are many reasons why such conditions are common. Financial barriers are frequently cited, together with lack of service access, cultural factors, global risk factors and social determinants. While recognising their importance, this proposal does not address these influences, but rather focuses on the role of oral health, specifically periodontal disease, in Aboriginal renal health.

### Chronic kidney disease (CKD); the problem

CKD is characterised by a progressive loss of renal function over a period of months or years culminating with end stage kidney disease (ESKD), when a person will require ongoing dialysis or a kidney transplant to stay alive, being the final stage of this progressive loss [5]. Like most other chronic diseases, the burden of CKD and consequent ESKD in Australia is increasing. It is estimated that approximately 12 % of Australians have either reduced kidney function or other markers of kidney damage [6]. There is clear evidence across the spectrum of CKD of an excess burden of premature comorbidity and mortality due to cardiovascular disease (CVD). CKD contributes to approximately 15 % of total Australian hospitalisations, with current medical costs for ESKD patients amounting to more than $1 billion annually [7]. Overall, patients with CKD have a mortality rate around 4 times that of their non-CKD counterparts [8].

### CKD; the measurement

Common measures used in the assessment of CKD are the urinary albumin-to-creatinine ratio (ACR) and glomerular filtration rate (GFR). Albuminuria (or microalbuminuria) is defined as urine ACR ≥3 and ≤30 mg/mmol, while proteinuria (macroalbuminuria) is defined as ACR ≥ 30 mg/mmol [9]. Because GFR cannot be directly measured in usual clinical practice, it is estimated from equations using serum creatinine, age, sex and body size [10]. Estimated GFR is referred to as eGFR. Both reduced eGFR and level of proteinuria are independent risk factors for CVD morbidity and mortality, and for progression of ESKD.

### CKD among Aboriginal Australians

Findings from the 2012–13 Australian Aboriginal and Torres Strait Islander Health Survey indicate that the prevalence of CKD amongst Australian Indigenous adults is approximately 18 % [11]. The National Biomedical Risk Factor Survey (which included approximately 3300 Indigenous adults) revealed that the prevalence of CKD was 34 % in remote locations, and that approximately 53 % of people with diabetes had signs of CKD. In Central Australia, more than 40 % of Aboriginal Health Service attendees were reported as having micro or macroalbuminuria and 40 % were reported as having reduced eGFR [12]. Dialysis is the leading cause of hospitalisation for Aboriginal Australians—constituting 42 % of all admissions [8]. Recent literature suggests that the prevalence nationwide of Aboriginal Australians with ESKD resulting in renal replacement therapy is around 10 times that of non-Aboriginal Australians [4]. Aboriginal Australians with ESKD are younger than their non-Aboriginal counterparts and there is high comorbidity. There is regional variability, with Aboriginal Australians living in remote Northern Territory communities having 20 times the prevalence of renal replacement therapy than remote-living non-Aboriginal Australians [13, 14]. Renal replacement therapy is strongly associated with socio-economic disadvantage [15, 16].

### Periodontal disease

Periodontal disease is inflammation of the tissues surrounding teeth and results from a complex interplay between bacteria and host risk factors. Periodontal organisms flourish in the presence of inflammation, enabling them to invade host tissues and to gain direct access to the circulation [17]. The constant exposure of the vasculature to these pathogens provides an opportunity for endothelial inflammatory activation and functional impairment [18]. Clinically, this manifests as deepening of the epithelial attachment around teeth, loss of periodontal attachment and, ultimately, tooth loosening. The total burden of this infection may be significant; specifically, it may account for a portion of the proposed risk for CKD and other systemic conditions that share an underlying inflammatory response as a common component of pathogenesis [17].

### Periodontal disease and Aboriginal Australians

Although representative national-level data are unavailable, estimates from convenience samples indicate that periodontal disease is a substantial problem among Aboriginal Australians. The prevalence of periodontal disease among Aboriginal participants seeking care at the Redfern Aboriginal Medical Service was around 60 % [19], while the prevalence was approximately 90 % in a recent convenience sample in the Northern Territory [20].

### CKD and periodontal disease

Periodontal disease has emerged as a non-traditional risk factor for CKD [21]. In nationally-representative cross-sectional surveys, there is increasing evidence of associations between CKD and periodontal disease, with a higher proportion of those with CKD having periodontal disease and vice versa [22–24]. Biological plausibility for considering periodontal disease as a CKD risk factor is derived from the potential role of the inflammatory response to periodontal disease in the chronic systemic inflammatory burden (for example, increased C-reactive protein (CRP) levels) associated with CKD [25–28]. The local tissue destructive immuno-inflammatory response to periodontal pathogens, their products and inflammatory cytokines are believed to contribute to the chronic systemic inflammatory burden of periodontal disease [29, 30].

### Can CKD progression be reduced by periodontal therapy?

Few studies have investigated the effect of periodontal treatment on kidney function. In a prospective cohort of haemodialysis patients in Thailand, successful non-surgical periodontal treatment resulted in marked reductions in CRP (mean change −3.2 mg/L) after two months [31]. A similar reduction in CRP following periodontal treatment was reported among patients with CKD in an Italian-based study (mean change −2.1 mg/L) [31]. Graziani and colleagues, in a prospective cohort including 20 healthy people, reported that successful periodontal treatment improved cystatin C levels but had no effect on eGFR after 3 months (mean change −1.4 mL/min/1.73 m^2^) [32]. In a non-randomised clinical trial involving 40 people, Artese et al. reported that periodontal therapy significantly improved eGFR among patients with CKD (mean change 4.2 mL/min/1.73 m^2^), whereas there were no differences in serum creatinine [33]. A reduction in proteinuria was obtained following a periodontal intervention among 11 patients with IgA nephropathy, but all patients were children [34]. There are substantial shortcomings with each of these studies; all have small sample sizes, most have only one periodontal therapy session and none were randomised controlled trials. There are also considerable differences in patient populations; the severity of CKD among our Aboriginal group will be greater, suggesting the possibility of increased efficacy of the periodontal treatment. Shortcomings aside, the evidence suggests that periodontal health may improve renal health, warranting a more robust clinical trial study design.

### Can CVD progression be reduced by periodontal therapy?

There is some evidence that CVD is influenced by periodontal health. Piconi et al. reported a diminution in carotid intima media thickness (cIMT; an established, non-invasive measure of atherosclerotic burden previously validated against histology specimens. cIMT is associated with cardiac risk factors, and predicts incident cardiovascular events) [35–39] 12 months following periodontal treatment among 35 otherwise healthy adults (mean change −0.12 mm, *P* < 0.001) [38]. In our recent periodontal intervention among Aboriginal adults in the Northern Territory, cIMT decreased in those randomised to the periodontal intervention (−0.026 mm [95 % CI −0.048, −0.003], *P* = 0.03) compared to control group [39]. The magnitude of the reduction in carotid IMT with periodontal intervention in this trial was equivalent to the effects of reversal of 4 years of aging, 8 kg/m^2^ lower body mass index or 25 mmHg lower systolic blood pressure. Mercanoglu and colleagues provided the first evidence that treating periodontal disease results in a functional improvement in cardiovascular status [40]. Among 54 otherwise healthy patients, flow mediated dilation (FMD)—a measure of endothelial function representing an important early stage of atherosclerosis [41], with its presence in coronary or peripheral vessels constituting an independent predictor of cardiovascular events [42], improved from 8.4 % to 17.7 % 6 weeks post periodontal treatment (*P* < 0.01). In an RCT, Tonetti et al. demonstrated improved FMD after 2 months (absolute difference 0.9 %; *P* = 0.02) and 6 months (absolute difference 2.0 %; *P* < 0.001) for the intervention group who received intense periodontal therapy [43]. The degree of improvement was associated with improvement in measures of periodontal disease (r = 0.29, *P* = 0.003).

### Aims and hypotheses

The goals are to assess levels of periodontal disease among a group of Aboriginal adults with CKD and to determine if comprehensive periodontal therapy might reduce progression of CKD, non-invasive measures of cardiovascular disease (CVD) or CKD/CVD-related death amongst people with CKD over 6 to 24 months. The specific aims and hypotheses are:Aim 1: To describe the extent and severity of periodontal disease in a group of Aboriginal adults with CKD.*Hypothesis: The extent and severity of periodontal disease in an Aboriginal population with CKD will be high compared with national-level indicators.*Aim 2: To examine the effects of a comprehensive periodontal intervention among an Aboriginal population with CKD.*Hypothesis: Exposure to a comprehensive periodontal intervention will reduce progression of CKD, non-invasive measures of CVD or CKD/CVD-related death amongst those with CKD.*

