### Inclusion criteria

Aboriginal people aged 18+ years who have lived in the study location for 2+ years, and who plan to live at their current location for the next 2 years, with CKD (i. on dialysis; ii. eGFR levels of <60 mls/min/1.73 m^2^ (CKD Stages 3 to 5); iii. ACR ≥30 mg/mmol irrespective of eGFR (CKD Stages 1 and 2); iv. diabetes plus albuminuria (ACR ≥ 3 mg/mmol) irrespective of eGFR), with at least 12 teeth at baseline and having moderate or severe periodontal disease will be invited to take part in the study. Periodontal disease will be assessed using the US Centers for Disease Control and Prevention and the American Academy of Periodontology definitions, whereby a case of moderate periodontitis is considered as the presence of either two sites between adjacent teeth with 4 mm + attachment loss or at least two such sites with 5 mm + pockets, and severe periodontitis as having at least two sites between adjacent teeth with 6 mm + attachment loss and at least one 5 mm + pocket [44].

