### Sample size

Based on a recent study of Australian Aboriginal adults with periodontal disease, it was estimated that a sample size of 472 would be necessary to detect a difference in cIMT of 0.026 mm (SD 0.09) [46] at the significance criterion of 0.05 and a power of 0.80. Allowing for 20 % attrition, 592 participants would be necessary at baseline, rounded to 600 for convenience.

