### Data analysis

Data analysis will use intention-to-treat and per-protocol approaches, with the effect on primary outcomes based on intention-to-treat analyses. Analyses will follow a general course of descriptive statistics such as distributions and measures of association. Simple cross-tabulations and more elaborate repeated-measures analyses will follow. In brief, the plan for the analysis of each aim is:*Aim 1: Extent and severity of periodontal disease compared with national-level counterparts:* Extent of periodontal disease will be defined by the number of periodontal sites in the mouth with a given pocket depth (PD) divided by the number of teeth in the mouth x 100. The National Survey of Adult Oral Health dataset will enable comparison with both general and Aboriginal population-level estimates [49]. General analysis will comprise Chi-square and Student’s t-test within the study sample and non-overlapping 95 % confidence intervals when comparing with population estimates.*Aim 2: Changes in cIMT, measures of renal function and CKD/CVD-related death:* The primary analysis will compare changes in cIMT and 95 % confidence intervals. Secondary analyses will examine each outcome variable using separate mixed models, to allow inclusion of all participants without having to impute data. We will use generalised linear mixed models for non-continuous outcomes. Models will include treatment group as a fixed effect. Analyses will be conducted to identify subgroups that modify the response to the intervention (eg. active/passive smoking, socio-economic status). Model assumptions will be checked and appropriate adjustments made. We will conduct sensitivity analyses to assess uncertainty in key parameters. Death and cardiovascular events, both binary outcomes, will be analysed using the chi-square test with frequencies and percentages per treatment arm and odds-ratios or other measures of treatment effect reported along with summary measures. The Greenhouse-Geisser correction for the F-test will be used to adjust the degrees of freedom for deviation from sphericity. Logarithmic transformation of the data will be performed where appropriate. A post hoc correlation analysis by the Spearman rank-correlation method will be performed to evaluate the relationship between the changes in renal function and cIMT from baseline to 6, 12 and 24 months following periodontal therapy. The same will also be done for measures of periodontal health and cIMT. Effect sizes will be calculated by dividing the mean of change scores by the pooled estimate of the standard deviation. Effect measures will also be presented through calculation of number-needed-to-treat and its associated 95 % confidence interval. The statistically significant level will be at α < 0.05.

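### Aim 1 compares a sample enrolled for having periodontal disease with unrestricted population estimates, so the comparison is biased towards its own hypothesis

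*Protocol article*

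**What the plan says.** Under Aims and hypotheses, Aim 1 is "To describe the extent and severity of periodontal disease in a group of Aboriginal adults with CKD". Its hypothesis is directional: "The extent and severity of periodontal disease in an Aboriginal population with CKD will be high compared with national-level indicators". Neither sentence mentions selection on periodontal status.

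Under Inclusion criteria, people with CKD "with at least 12 teeth at baseline and having moderate or severe periodontal disease will be invited to take part in the study". The case definition there rests on a small number of affected sites: "a case of moderate periodontitis is considered as the presence of either two sites between adjacent teeth" that reach an attachment-loss threshold of 4 mm, or at least two that reach a pocket threshold of 5 mm. Severe disease needs at least two sites with 6 mm attachment loss plus at least one 5 mm pocket.

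Under Data analysis, the Aim 1 measure is extent: "Extent of periodontal disease will be defined by the number of periodontal sites in the mouth with a given pocket depth", divided by the number of teeth and multiplied by 100. The comparator is the national survey: "The National Survey of Adult Oral Health dataset will enable comparison with both general and Aboriginal population-level estimates". The criterion is non-overlapping 95% "confidence intervals when comparing with population estimates".

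No section restricts the survey comparator to periodontitis cases or to people with 12 or more teeth. No section describes an Aim 1 analysis of people with CKD who were not selected on periodontal status.

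**The concern.** The entry rule and the Aim 1 outcome are the same disease. Everyone in the sample is a case, whereas a population-level estimate averages over cases and non-cases. The two would differ even if periodontal disease were distributed identically among Aboriginal adults with CKD and in the comparator population, and the difference would run in the hypothesised direction.

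At stake is a published statement that this population's disease burden is high by national standards, when part or all of the excess could come from the enrolment rule. The 12-tooth minimum is a second restriction that the comparator is not said to share.

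**Working it through.** **No plan figure to reproduce.** The protocol gives no sample size, effect size or expected value for Aim 1. The check is one of logic, followed by the size of the bias when there is no true difference.

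**Inputs**
- Planned enrolment from Sample size: 592 "participants would be necessary at baseline, rounded to 600 for convenience".
- Prevalence of periodontal disease from the section on periodontal disease and Aboriginal Australians: about 60% and about 90%, in two convenience samples. That section does not say that these use the moderate-or-severe definition, and they are not the survey named as comparator.
- National case prevalence: not given. A range of 20% to 40% is assumed for illustration.

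**Step 1: prevalence.** By the entry rule, 600 of 600 participants have moderate or severe disease. The exact lower 95% limit is 0.025^(1/600) = 0.994. Any population estimate whose upper limit lies below 99.4% is exceeded automatically, whatever the truth about CKD.

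**Step 2: mean extent.** Let p be the proportion of the comparator population that meets the case definition, m1 the mean extent among cases and m0 the mean among non-cases. The population mean is p·m1 + (1 − p)·m0. With no true difference, and setting the tooth rule aside, the trial sample has mean m1. The ratio is

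m1 / [p·m1 + (1 − p)·m0]

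This exceeds 1 whenever m0 < m1 and p < 1. It reaches its maximum, 1/p, only if non-cases have zero extent (m0 = 0).

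| p | Upper bound 1/p | Source of p |
|---|---|---|
| 0.90 | 1/0.90 = 1.11 | protocol, convenience sample |
| 0.60 | 1/0.60 = 1.67 | protocol, convenience sample |
| 0.40 | 1/0.40 = 2.5 | assumed |
| 0.20 | 1/0.20 = 5.0 | assumed |

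**Step 3: how often the stated criterion would mislead.** A simulation gave the CKD and national populations the same distribution of affected sites (negative binomial, shape 0.5 or 1.0). It restricted the trial sample to people with two or more affected sites, then compared 600 of them with an assumed survey of 4,000 by non-overlapping 95% intervals, in 500 runs per setting.

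| p | Ratio of means (shape 0.5; 1.0) | Runs declaring the trial sample worse |
|---|---|---|
| 0.20 | 3.87; 3.46 | 100%; 100% |
| 0.40 | 2.31; 2.16 | 100%; 100% |
| 0.60 | 1.63; 1.58 | 100%; 100% |
| 0.90 | 1.11; 1.11 | 20%; 47% |

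The survey size and the distributions are assumptions. The simulation also counts sites without dividing by teeth, and it selects on the very sites it then counts. The protocol's link is looser: moderate disease can be met through attachment loss alone, so an eligible person may have no deep pocket and score zero on a deep-pocket extent measure. The percentages therefore illustrate the mechanism and are not forecasts.

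**Step 4: the 12-tooth rule.** Extent is expressed per tooth, and the protocol does not describe the tooth counts of survey respondents. The direction of this mismatch cannot be derived from the document.

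**The case against.** **Aim 1 is descriptive.** The aim only sets out to describe a group, and that description can be produced for those enrolled. This stands, and a reader who concludes that Aim 1 as a whole cannot be answered goes too far. What fails is the comparative hypothesis, which concerns an Aboriginal population with CKD and carries its own criterion.

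**The entry rule guarantees the result.** A reader might infer that eligibility alone confirms the hypothesis. That is true only for the prevalence of moderate or severe disease. The one measure that Data analysis defines is pocket-depth extent; the eligibility floor is two sites and need not involve pockets, so a higher mean extent is likely but not assured. At 90% comparator prevalence, the illustration misled in fewer than half of the runs.

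**The 12-tooth rule offsets the bias.** It is tempting to say that excluding people who have lost most of their teeth pulls the other way. The document does not establish this.

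**The hypothesis attributes the excess to CKD.** It does not. It says only that disease will be high relative to national indicators, so the criticism should not be that the trial claims a CKD effect.

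**Detail may sit elsewhere.** The article condenses a fuller protocol, introduces its analysis plan as a summary, and names the survey dataset, so a matched restriction could be made. But the eligibility rule, the hypothesis and the population-level comparator are all stated, and they do not fit together. A restriction set out elsewhere would change the comparison stated here, and the hypothesis would need rewording to match.

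**Conclusion.** The point holds for the external comparison in Aim 1. As written, it sets a sample selected on the outcome against estimates with no stated matching restriction, and it is biased towards the hypothesis. Excess prevalence of moderate or severe disease is automatic. Excess mean extent is likely, with inflation of at most 1/p: 1.1 to 1.7 at the protocol's 90% and 60%, and 2.5 to 5 at an assumed national 40% to 20%. These are upper bounds. They assume negligible extent among non-cases, no true difference between the populations, and that the quoted prevalences can stand in for the comparator's case prevalence.

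A reader might infer that the trial's main result is compromised. It is not: the cIMT primary outcome, the randomisation, the sample size and the rest of Aim 2 do not depend on this comparison. The matter should be fixed, but it does not threaten the trial.

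**What to change.** Apply the Inclusion criteria's case definition and the 12-tooth minimum to the national survey dataset, as far as its variables allow. Standardise the comparison for age and sex, both of which the trial collects at baseline. Restate the Aim 1 hypothesis as extent and severity among people with moderate or severe periodontitis.

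If the survey cannot support the restriction, drop the comparative hypothesis and report Aim 1 as a description of the enrolled group.

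This costs some analysis work and a change of wording. The claim becomes narrower, and the restricted comparator will be smaller and so less precise. Randomisation, treatment and sample size do not change.

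An alternative that keeps the broader question is to base Aim 1 on everyone with CKD who had the eligibility dental examination, including those who failed the periodontal or tooth criterion. It is available only if those people's data are kept with their consent.
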